### Social Return on Investment approach

Social Return on Investment (SROI) is one of the most well-known social impact methods (21) and has been regarded as the “nearest to a current industry standard for project or organisational level social impact reporting” [(24), p. 21]. SROI is an economic measurement tool used to apply a monetary value to socially situated outcomes (25, 26). It seeks to establish how inputs (e.g., staffing) are converted to outputs (including the activities undertaken to deliver the outcomes) and subsequent participant outcomes (e.g., an aspect of improved quality of life such as self-esteem or mental health).

A core feature of SROI methodology is the engagement of stakeholders to determine which outcomes are relevant and deemed to be most important. Another key feature of SROI methodology is to assign monetary values to program outcomes, which may not have market prices (27). As SROI seeks to monetize non-financial factors, there is a need to identify financial proxies that can be used to estimate the positive (or negative) social value created by participating in a given program (25, 26). Ultimately, SROI results in a ratio, such as 3:1, which in this instance shows that for every dollar invested in a program (or organisation), a social value of three dollars is created. The final SROI ratio is not intended to indicate financial value but instead conveys a social value currency (28).

SROI studies can play an important role in how social enterprises conceptualise, measure and communicate their achievements (23) and may be used by governments and philanthropists when making funding decisions (29). The SROI process can help organisations better understand the processes that impact their stakeholders by identifying the links between activities and impacts. As a relatively new methodology, it is important to be transparent about the SROI methodology applied, especially when developing some of the more ambiguous and challenging steps involved in the methodology, including measurement indicators and the proportion of the outcome that may have occurred without any intervention having occurred (28).

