The Theory was also informed by an existing Satellite program logic model but condensed to include only children and young people and to consider only the three programs targeted in the SROI. Specific outcomes generated from the resulting Theory of Change include (i) a sense of belonging and increased connectedness (ii) increased resilience, and (iii) a sense of hope, optimism and possibility. We also needed to consider potentially negative outcomes to ensure that we provide a true and fair picture that allows Satellite to continuously improve and assess trade-offs between outcomes. Potentially negative outcomes will be identified in the interviews with young people.

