#### Giving outcomes a value

In the final part of this process, we give the identified outcomes a monetary value using financial proxies that reflect that importance of the outcome to stakeholders (see Table 3). In consultation with the YAC, a sense of connectedness and sense of belonging was considered similar to having friends. Powedthavee (64) identified the economic value of making and having new friends, in addition to existing friends, and this value was subsequently updated and converted to Australian dollars (See Table 3). Given that the original value was calculated in 2007, we adjusted it for inflation to reflect its current purchasing power, ensuring consistency with contemporary economic conditions. Although using a currency converter may not be the ideal method, this approach, when combined with inflation adjustments, provides a reasonable approximation of the value in today’s terms.

**Table 3 tab3:** SROI stage 3 outcomes.

Stakeholder		Stage 3				
Satellite young person participants		The outcomes (what changes)				
	Outcome	How will we know if the outcome has occurred	Source	How can you value the change?	Value $AUD for six-month period	Source
		Measured how?	Where this information comes from	What proxy is used to value the change?	Value of the change	Where this information comes from
	Sense of belonging and increased connectedness	Feel more connected to other young people living in similar circumstances	SDQ: Prosocial behaviour subscale (child and parent versions) LSAC items on connectedness Interviews with children/youth	Powdthavee (64) identified the economic value of friends (in addition to existing friends): 15,500 pounds per year in 2007 is equivalent to 23,903.38 pounds in 2022, converted to 2022 AUD 42,818.76 *per annum*	$21,861.38	Powdthavee (64).
		Reduced feelings of isolation and increased feelings of belonging				
	Increased resilience	Decreased mental health crises	CYRM-R total score KCS, completed by children aged 10 years and under; CASQ, completed by older children, adolescents and young adults Interviews with children/youth	The Australian Psychological Society (APS) recommends $300 per hour per child/young person for psychological services – 14 sessions	$4,200 per child/young person	APS website: https://psychology.org.au/psychology/about-psychology/what-it-costs

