An *a priori* power analysis was conducted using G*Power version 3.1.9.7 software (65) to determine the minimum sample size required for the study. The required sample size to achieve 80% power for detecting a medium effect at a significance criterion of *α* = 0.05 will be 29 per group {intervention [Satellite participants] and usual care [LSAC]; as per (30)}. Other deadweight measures will be ascertained by asking young people what they perceive would have happened if they had not attended Satellite and their estimation of the impact of that occurrence (in the interviews). This is necessary as there is a risk that LSAC participants may be engaged in programs similar to Satellite. Their responses will be used to inform and qualify any differences between the LSAC calculations and the Satellite participant sample as well as deadweight across other age groups and for other outcome measures not included in the LSAC data set.

Displacement is an assessment of how much the outcome might have displaced other outcomes, including the occurrence of negative outcomes for the children and young people and others. An evaluation of a similar program {Paying Attention to Self [PATS]; (57)} found that building new connections with participants during the program came at the cost of building peer relationships in other sites outside the program such as school and this is a concern that could apply here. Alternatively, participants could be gaining transferrable social skills at Satellite that then lead to better connections at school and other settings. We will be investigating this and other potential outcomes in the conversations with young people and who they are turning to.

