### Duration and drop off

Duration refers to how long an outcome lasts for, while drop off acknowledges that outcomes may continue to last for many years but may decrease over time, or if it is sustained, may be influenced by other factors. To calculate drop off, we will deduct a fixed percentage from the remaining level of outcome at the end of 6 months. This decision will be based on the longitudinal interviews, which follow young people over the course of the project, including those who have maintained a relationship with Satellite and those who have not.

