## Calculating the SROI

Calculating the SROI involves adding up the outcomes (value), applying the discounts (attribution, displacement, deadweight and drop off) and comparing the result to the investment or costs incurred in delivering the program. Costs involved for Satellite involve employing staff to facilitate programs (including administration and registration), insurance, venue hire, catering, materials and travel (Satellite sometimes pays for transport so that young people/children can attend programs). Expenses associated with reimbursing YAC members for their input and advice on the programs offered is also included. Our analysis spanned a six -month period only (as indicated in Table 3), which does not necessitate the use of a discount rate to account for the time value of money (58). As the timeframe is less than a year, no additional adjustments for the differing value of money over time were required.

Once the net present value of costs and outcomes have been established (taking into consideration drop off, deadweight and displacement), the final ratio can be calculated. The formula for calculating the return on investment is:

SROI ratio = Social value of stakeholder outcomes (discounted)

Cost of providing programs

According to Arvidson et al. (23), an SROI ratio greater than one indicates a positive return on investment, or in other words, where the benefits of the investment are greater than its costs. The calculation is based on proxy values, as outlined in Table 3.

As the results are influenced by non-quantitative variables and assumptions, a sensitivity analysis for the SROI will be calculated to promote robustness. After establishing a base case scenario as outlined above, each key assumption will be changed (by ±10%), one at a time, to ascertain how much the SROI ratio changes. Changes in the SROI will be compared for each variation and those assumptions that cause the most significant changes in the SROI ratio identified. Several plausible scenarios will be developed including best case, worse case and moderate scenarios, using most optimistic to most pessimistic values of each of the assumptions. Each of these scenarios will be reported including a discussion of which assumptions have the most significant impact on the SROI ratio.

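### Negative outcomes have no priced line in Table 3 and enter the calculation only through displacement, a discount on gains, so on the natural reading the ratio cannot show a net loss

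*Protocol article*

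**What the plan says.** All references are to the protocol article.

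- **Aim.** Under Social Return on Investment approach, proxies are said to "estimate the positive (or negative) social value created by participating in a given program". Under Mapping outcomes the authors write: "We also needed to consider potentially negative outcomes to ensure that we provide a true and fair picture". Establishing scope and identifying stakeholders also cites the principle that change in either direction belongs in the analysis.
- **Finding harm.** Mapping outcomes states: "Potentially negative outcomes will be identified in the interviews with young people".
- **Pricing.** Table 3 has three rows, all gains: belonging and connectedness at AUD 21,861.38 for six months, resilience at AUD "4,200 per child/young person", and hope at AUD 1,250. Calculating the SROI states: "The calculation is based on proxy values, as outlined in Table 3".
- **Where harm enters.** Deadweight and displacement defines displacement as "how much the outcome might have displaced other outcomes, including the occurrence of negative outcomes for the children and young people and others". Calculating the SROI adds up outcome value and then proceeds by "applying the discounts (attribution, displacement, deadweight and drop off".
- **Form of the discounts.** Only drop off has a stated form: "we will deduct a fixed percentage from the remaining level of outcome at the end of 6 months". The form of displacement is not given.

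**The concern.** A discount modifies a value that already exists. If harm is handled only as a discount on gains, its weight depends on how much other participants gained and not on how many were harmed or how badly. A harm that does not mirror one of the three credited outcomes has no dollar figure anywhere in the plan. If harm were to exceed gain, a proportional discount could take the numerator to zero but not below it. The plan would then collect evidence of harm that its main result could not fully express, contrary to its own aim.

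The Conclusion foresees the findings being used to seek funding, so a result that cannot register net loss matters most for a weak or harmful program. The planned sensitivity analysis varies existing assumptions one at a time by 10% and then in scenarios. Neither adds a missing negative line, and Limitations does not mention the gap.

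**Working it through.** **Inputs.** The article states no displacement rate, harm count, harm value or SROI ratio, so there is no ratio to reproduce. The three proxies come from Table 3 and can be checked:

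- Resilience: 14 × 300 = 4,200, as printed.
- Hope: 2,500 / 2 = 1,250, as printed.
- Belonging and connectedness: 42,818.76 / 2 = 21,409.38, against a printed 21,861.38 (difference 452.00). The printed value is used below, and the difference does not affect this point.

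Sum of the proxies: V = 21,861.38 + 4,200 + 1,250 = AUD 27,311.38.

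**Assumptions for illustration only.** There are 100 participants. *g* gain all three outcomes, *h* are harmed by an equal and opposite amount, and the rest do not change. Other discounts are zero.

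- Reading A, proportional discount on counted gains: g × V × (1 − d), with d from 0 to 100%.
- Reading B, harm as its own signed line: (g − h) × V.

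| g | h | A, d = 0% | A, d = 10% | A, d = 30% | A, d = 100% | B |
|---|---|---|---|---|---|---|
| 60 | 10 | 1,638,683 | 1,474,815 | 1,147,078 | 0 | 1,365,569 |
| 60 | 20 | 1,638,683 | 1,474,815 | 1,147,078 | 0 | 1,092,455 |
| 60 | 40 | 1,638,683 | 1,474,815 | 1,147,078 | 0 | 546,228 |
| 30 | 40 | 819,341 | 737,407 | 573,539 | 0 | −273,114 |
| 0 | 40 | 0 | 0 | 0 | 0 | −1,092,455 |

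**Can a discount reproduce the net?** Setting A equal to B gives d = h / g.

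- For 60 gainers and 20 harmed, d = 20/60 = 33.3%, and 60 × V × (1 − 20/60) = 40 × V = 1,092,455, the same as B.
- For 30 gainers and 40 harmed, d = 40/30 = 133%, which is outside the range of a discount.
- For no gainers, no value of d works.

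So when harm is no larger than gain, a well-chosen discount can give the right net. Choosing it requires the number harmed and the price of the harm, which is the content of the row that Table 3 lacks.

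**Reading C, signed net change.** If value is 100 × mean change × V, a mean change of −0.1 proxy units gives 100 × (−0.1) × 27,311.38 = −273,114. The numerator can then be negative. A 10% discount turns this into −245,802, which is a smaller loss. Under signed counting, leaving harm inside a proportional discount would therefore move a negative result towards zero.

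**The case against.** **A reader might infer that the numerator can never fall below zero.** The article does not establish this. It needs two unstated conditions: displacement is a percentage of at most 100%, and only gainers are counted. A dollar deduction would fit the word discount. The within-subject pre-post design and the repeated-measures analysis estimate change that can be negative, as in reading C. How scores become counted outcomes may be set out in the full plan. This objection stands, and the zero floor is conditional. Reading A remains the more natural one: Table 3 values outcomes as flat sums with indicators worded as improvement, the one discount whose form is given is a percentage, and a dollar deduction would need a price for harm that Table 3 does not supply.

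**A reader might infer that a harmed participant who gains nothing subtracts nothing.** This also goes too far. The definition of displacement covers young people and others generally, so that person could raise the rate applied to everyone else's gains. The effect still scales with those gains and disappears when there are none.

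**A reader might fix displacement at, say, 10% and quote the resulting overstatement.** The article sets no such rate. If displacement is assessed from the harm found, the rate should rise with it, and h / g reproduces the signed net whenever harm does not exceed gain.

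**Rows for harm cannot be expected yet.** This is a forecast SROI, and harms are to be found in interviews. That explains why no row exists today. It does not explain why the stated destination for harm is a discount instead of a valued line, and worsening on the three measured outcomes can be foreseen now.

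**Conclusion.** The point holds in a conditional form. It is certain from the text that Table 3 prices only gains and that displacement, a discount on summed value, is the only calculation step naming negative outcomes. This conflicts with the article's aim of valuing change in both directions.

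If displacement is proportional and gains alone are counted, harm is not valued in its own right, unrelated harm has no price, and the numerator cannot show a net loss. In the assumed case of 30 gainers and 40 harmed, the gap between the signed result and the discounted one is between 273,114 (d = 100%) and 1,092,455 (d = 0%: 819,341 + 273,114). Those figures rest on assumed counts and on harm priced equal to gain. They show the mechanism and do not estimate the error in this study. No general overstatement can be claimed when harm is smaller than gain.

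**What to change.** 1. Remove negative outcomes from the definition of displacement, and keep displacement for benefit moved from elsewhere, such as the article's example of peer ties built in the program at the expense of ties at school.
2. State that each negative outcome identified will receive its own Table 3 row with the number affected and a proxy, subtracted in the numerator before the ratio is formed.
3. For the three measured outcomes, state that change is counted with its sign, as net change. Net change is preferable to counting individual decliners, because measurement noise would otherwise be booked as harm; the Kids Coping Scale, for example, has a reported internal consistency of 0.30 to 0.58.
4. Use the same proxy for loss as for gain only as a declared assumption, and vary it in the sensitivity analysis. Nothing in the article shows that losing connectedness costs what gaining it is worth.

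The cost is some extra rows, one subtraction and a written counting rule. The three measured outcomes need no new data collection. The downside is that the ratio may fall, and a proxy must be justified for any harm outside those outcomes.

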### Attribution

Attribution is a consideration of who else could have contributed to the outcomes, which helps to identify stakeholders and activities that can also play a role in change. This could be, for example, a young person who attended Satellite but also received sessions from a psychologist or took medication for their own mental health challenges. We are addressing attribution by controlling for children and young people who have participated in programs in the past at baseline, compared with those who are new to Satellite. This will account for the differences in their lived experience before starting their next/first program. We are also asking participants if they have accessed carer services and/or health professionals in the last 6 months at each time point, so that those who engage with more than one service and/or health professional can be accounted for as well.

### Duration and drop off

Duration refers to how long an outcome lasts for, while drop off acknowledges that outcomes may continue to last for many years but may decrease over time, or if it is sustained, may be influenced by other factors. To calculate drop off, we will deduct a fixed percentage from the remaining level of outcome at the end of 6 months. This decision will be based on the longitudinal interviews, which follow young people over the course of the project, including those who have maintained a relationship with Satellite and those who have not.

## Calculating the SROI

Calculating the SROI involves adding up the outcomes (value), applying the discounts (attribution, displacement, deadweight and drop off) and comparing the result to the investment or costs incurred in delivering the program. Costs involved for Satellite involve employing staff to facilitate programs (including administration and registration), insurance, venue hire, catering, materials and travel (Satellite sometimes pays for transport so that young people/children can attend programs). Expenses associated with reimbursing YAC members for their input and advice on the programs offered is also included. Our analysis spanned a six -month period only (as indicated in Table 3), which does not necessitate the use of a discount rate to account for the time value of money (58). As the timeframe is less than a year, no additional adjustments for the differing value of money over time were required.

Once the net present value of costs and outcomes have been established (taking into consideration drop off, deadweight and displacement), the final ratio can be calculated. The formula for calculating the return on investment is:

SROI ratio = Social value of stakeholder outcomes (discounted)

Cost of providing programs

According to Arvidson et al. (23), an SROI ratio greater than one indicates a positive return on investment, or in other words, where the benefits of the investment are greater than its costs. The calculation is based on proxy values, as outlined in Table 3.

As the results are influenced by non-quantitative variables and assumptions, a sensitivity analysis for the SROI will be calculated to promote robustness. After establishing a base case scenario as outlined above, each key assumption will be changed (by ±10%), one at a time, to ascertain how much the SROI ratio changes. Changes in the SROI will be compared for each variation and those assumptions that cause the most significant changes in the SROI ratio identified. Several plausible scenarios will be developed including best case, worse case and moderate scenarios, using most optimistic to most pessimistic values of each of the assumptions. Each of these scenarios will be reported including a discussion of which assumptions have the most significant impact on the SROI ratio.

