***Resilience*** will be measured by the total score of the Children and Youth Resilience Measure – Revised [CYRM-R; (37)]. Resilience in this context is defined as “the capacity of individuals to navigate their way to the psychological, social, cultural, and physical resources that sustain their well-being, and their capacity individually and collectively to negotiate for these resources to be provided in culturally meaningful ways” [(38); p. 225]. The CYRM-R is a 17 item self-report measure of social-ecological resilience. Participants respond to the items using a 5-point Likert scale from *not at all* to *a lot*, e.g., “I know how to behave/act in different situations.” The CYRM-R has good internal consistency (*α* = 0.82) and a Rasch analysis indicated that both subscales have good ability to discriminate between people with varying levels of resilience (67).

Given the Theory of Change (Figure 1) which positions adaptive coping as an intermediate outcome leading to resilience, two coping measures will also be used to evidence resilience; the Kids Coping Scale [KCS, completed by children aged 10 years and under; (39)] and the Coping Across Situations Questionnaire [CASQ, completed by older children, adolescents and young adults; (40)]. The KCS has nine items with two subscales: emotion-focused and problem-focused coping. Children answer the items, e.g., “You avoided the problem or where it happened” using a three-point Likert scale (never, sometimes, a lot). The KCS has fair internal consistency (*α* = 0.30–0.58). It is acknowledged that the KCS has relatively low reliability. However, it should be noted that there is a lack of validated measures on coping for young children especially those who are at risk for their own mental health difficulties (41). A similar measure has been developed more recently, i.e., the Coping Questionnaire Child (42) which reports fair reliability (α = 0.68) and has fewer items. However, the measure involves children responding to vignettes relating to anxiety-provoking situations that are read to them by an examiner. We chose the KCS as it employed simple language, allowed children to complete the measure independently, and related to their general coping styles rather than specific anxiety-provoking situations. This is acknowledged to be a limitation of the project.

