The CASQ has 20 items which measure coping strategies across three different areas: active (using social resources to solve problems), internal (appraising situations and searching for a compromise) and withdrawal (avoiding the situation) e.g., “I try to get help and comfort from people who are in a similar situation.” Young people rate each item on a 5 point Likert scale from *not used* to *always used*. The CASQ has fair to good internal consistency (*α* = 0.73–0.80) and moderate to strong test–retest reliability over 1 year (*r* = 0.47–0.88).

A sense of ***hope***, ***optimism and possibility*** will be measured using the Children’s Hope Scale [CHS; (43)]. The scale assesses whether children can identify a means to carry out goals (pathways) and their ability to initiate and sustain action towards goals [agency; (43)]. The measure is comprised of six self-report items rated on a 6-point Likert- scale (from not at all to all of the time) e.g., “Even when others want to quit, I know that I can find ways to solve the problem.” Scores can range from 6 to 36, with higher scores indicative of greater agency and goal attainment. The CHS has fair to good internal consistency (*α* = 0.72–0.86) and strong test re-test reliability over 1 month [*r* = 0.71; (43)].

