	Sense of hope, optimism and possibility	Increased hope for the future that results in planning for future activities/goals, agency	Children’s Hope Scale Interviews with children/youth	Cost of a mentor such as what might be available from the Big Brothers, Big Sisters mentoring program: $2,500 per person for 12 months	$1,250	Big Brother, Big Sisters of Australia Annual Report 2019–2020 BBBS_Annual_Report_2019-2020.pdf (bigbrothersbigsisters.org.au)

We also identified a financial proxy for resilience. For the young people involved in these programs, resilience refers to achieving positive outcomes (inclusive of wellbeing) despite coming from challenging backgrounds, and adaptively coping with current stressors (see Figure 1, Theory of Change). According to Olsson et al. (48), promoting resilience at an individual level involves developing personal coping skills and resources, both of which they suggest may be obtained from one to one therapy. Pascual-Leone et al. (49) suggested 14 individual sessions is appropriate for individuals with existing issues. It was on this basis that resilience was valued as 14 individual, psychotherapeutic sessions (see Table 3). The assumption that 14 individual psychotherapeutic sessions has a similar effect to a one-day workshop (e.g., the Create and Connect program) is admittedly contestable. However, a one-day workshop that focuses on creativity and connectedness can offer an intensive, immersive experience that might be considered similar to the impact of multiple counselling sessions (33, 50). Moreover, the unique therapeutic mechanisms of creative programs can lead to profound insights and emotional processing (51–53), potentially achieving in 1 day what might take multiple counselling sessions. The added dimension of group dynamics in these programs which emphasises peer support, can amplify the overall therapeutic impact (33, 50, 51), again potentially contributing to outcomes comparable to multiple individual counselling sessions.

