The final outcome involves an increased sense of hope, optimism and possibility, which has been equated to future planning and projecting oneself into the future (54). In identifying a comparable proxy, we are suggesting that the programs offered by Satellite are comparable to having a mentor. Mentors help with goal setting and guidance with planning to achieve those goals; mentors also help young people navigate challenges, make important decisions, and offer advice on various aspects of life (55). Thus, in valuing this outcome, we are equating having a mentor to participating in Satellite programs, which likewise aim to build young people’s hope, optimism and a sense of possibility.

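### The three priced outcomes are added with no allowance for overlap between them, so one gain may be credited twice and the ratio may be overstated by up to about 25%

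*Protocol article*

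**What the plan says.** Calculating the SROI gives the rule: the numerator is formed by "adding up the outcomes (value), applying the discounts (attribution, displacement, deadweight and drop off"), and the result is set against the cost of the programmes. The values come from Table 3 (Giving outcomes a value):

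- Connectedness and belonging: a friendship value, "converted to 2022 AUD 42,818.76" a year, entered as AUD 21,861.38 for six months.
- Resilience: 14 therapy sessions, AUD "4,200 per child/young person".
- Hope, optimism and possibility: a mentor at AUD "2,500 per person for 12 months", entered as AUD 1,250.

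Establishing impact defines the four deductions. Deadweight is change expected without the programme, displacement is other outcomes pushed aside, attribution is what others contributed, and drop off is decay over time.

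The sensitivity analysis moves each key assumption by 10% in either direction, one at a time, and adds best, worst and moderate scenarios. Overlap between outcomes is not named as an assumption there or under Limitations.

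**The concern.** Adding three values is sound if they price three separate gains. The article's own text suggests that they are partly the same gain.

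**Connectedness and resilience.** Table 3's first indicator of connectedness is "Feel more connected to other young people living in similar circumstances". Resilience is defined as the capacity to "navigate their way to the psychological, social, cultural, and physical resources that sustain their well-being", so social resources are one of four kinds named. The CASQ, listed as evidence of resilience, has an active-coping area about drawing on social resources, and its illustrative item is "I try to get help and comfort from people who are in a similar situation". The therapy proxy is itself defended partly by the workshops' attention to connection and by peer support within the group. Connection is thus part of the reason for claiming AUD 4,200 and is also priced separately.

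**Resilience and hope.** The illustrative Children's Hope Scale item concerns finding ways to solve a problem, while resilience is evidenced partly by problem-focused and active coping. The mentor proxy for hope rests partly on the statement that "mentors also help young people navigate challenges, make important decisions, and offer advice on various aspects of life". That is close to the article's account of resilience as coping adaptively with current stressors.

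The ratio is the headline result, and the Conclusion expects it to be used in seeking government and philanthropic funding. The article also adopts a principle against overclaiming. A numerator that may count a gain twice, with no scenario showing how much this matters, sits badly with that principle.

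**Working it through.** **Inputs (Table 3).** Connectedness C = 21,861.38, resilience R = 4,200, hope H = 1,250, all in AUD for six months.

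**Reproducing the table.**
- R: 14 × 300 = 4,200, as stated.
- H: 2,500 / 2 = 1,250, as stated.
- C: 42,818.76 / 2 = 21,409.38, against 21,861.38 stated. The difference is 452.00, or 2.1%. This is a separate point; the stated value is used below and the halved value is checked at the end.

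**Planned sum** for a participant credited with all three, before deductions:
C + R + H = 21,861.38 + 4,200 + 1,250 = 27,311.38. The shares are 80.0%, 15.4% and 4.6%.

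**Effect of overlap.** Let q be the share of R + H = 5,450 already contained in a larger proxy. The article gives no value for q, so the full range 0 to 1 is shown. The larger proxy is kept for any shared gain.

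Inflation = 27,311.38 / (27,311.38 − q × 5,450) − 1

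| q | Value without duplication (AUD) | Inflation |
|---|---|---|
| 0 | 27,311.38 | 0% |
| 0.10 | 26,766.38 | 2.0% |
| 0.25 | 25,948.88 | 5.3% |
| 0.50 | 24,586.38 | 11.1% |
| 0.75 | 23,223.88 | 17.6% |
| 1.00 | 21,861.38 | 24.9% |

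At q = 1 the duplicate part is 5,450 / 27,311.38 = 20.0% of the planned sum. Programme cost cancels in the relative change. The deductions also cancel if they are the same proportion for each outcome, which is assumed here.

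**One pair at a time, complete overlap.**
- Connectedness and resilience only: 27,311.38 / (21,861.38 + 1,250) = 1.182, or 18.2%.
- Resilience and hope only: 27,311.38 / (21,861.38 + 4,200) = 1.048, or 4.8%.

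**Participants credited with fewer outcomes.** For resilience and hope without connectedness, the factor at complete overlap is 5,450 / 4,200 = 1.30, but the amount at issue is only AUD 1,250.

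**Does the planned sensitivity analysis reach this?** A 10% change in one proxy moves the sum by 0.1 × 21,861.38 / 27,311.38 = 8.0% for connectedness, 1.5% for resilience and 0.5% for hope. Complete overlap would lower it by 20.0%.

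**With C = 21,409.38.** The sum is 26,859.38 and the maximum inflation is 26,859.38 / 21,409.38 − 1 = 25.5%. The conclusion does not change.

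**The case against.** Related constructs are not the same gain. A young person can make friends and also cope better, and adding the two is then correct. The questionnaire evidence for overlap is thinner than the wording suggests. The CASQ item matches Table 3's descriptive indicator, not a connectedness scale. Connectedness is evidenced by the SDQ prosocial subscale, LSAC items and interviews; the one SDQ item shown is about giving help, not seeking it, and the LSAC items are not shown. Resilience is measured by the CYRM-R total, with coping measures as additional evidence. The CASQ item is one of 20, and children aged 10 and under complete the KCS instead. The article states no rule by which movement on one item earns the full proxy. The Theory of Change figure is not available here. Limitations argues against leaving out important outcomes, and restricting the analysis to young people may bias the ratio downward, as the article admits.

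Most of this stands, and it limits the claim to possible double credit of unknown size. It does not supply a deduction for shared value, and it does not answer the therapy proxy's reliance on connection and peer support. Nor does a separate, disclosed downward bias justify double counting. The article sets out the calculation rule itself, so this is not simply detail left to a fuller document.

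Three stronger readings are tempting but unsupported:

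- **That one gain is paid for three times.** No item, definition or rationale is common to all three outcomes, and any link between connectedness and hope is only indirect.
- **That the ratio is overstated as a matter of fact.** The overlapping share is unknown and could be zero.
- **That the authors merged connectedness, belonging and loneliness because they were alike, and so had already conceded the issue.** Mapping outcomes takes the similarity of those preferences as a sign of their importance; it does not give it as the reason for merging.

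**Conclusion.** The point holds as a possible overstatement. The three proxies are summed, none of the four deductions removes value shared between them, and the text shows partial overlap within two pairs of outcomes. For a participant credited with all three, the inflation from this source lies between 0% and about 25%, and is about 11% at half overlap. This rests on three assumptions: the larger proxy is kept for a shared gain, the deductions are proportionally equal across outcomes, and the overlapping share may lie anywhere from none to complete. The top of the range is an outer bound, because it also requires all of hope to lie within value already priced elsewhere. Since connectedness alone is 80% of the sum, overlap cannot double or triple that participant's value under these assumptions. The one-at-a-time 10% changes do not cover the range, and the best and worst scenarios would do so only if additivity were named among the assumptions they vary. This is a cheap improvement to the plan, not a fault that invalidates it.

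**What to change.** In Calculating the SROI:

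1. Name additivity of the three outcomes as a key assumption.
2. Keep the full sum, and label it the upper bound with respect to overlap.
3. Add a pre-stated lower scenario in which a participant who gains on several outcomes is credited with the highest single proxy only.
4. Report the correlations between the outcome change scores, so that readers can judge how far the gains move together. A correlation does not itself measure shared value, so it informs the choice between the bounds and does not replace them.

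The cost is one sentence, one scenario and one small table, from data already being collected. The downside is a less favourable lower figure beside the headline ratio. A highest-proxy base case is not required: it would treat complete overlap as the expected state and leave the friendship value to decide the result. Nor should CASQ items be removed, since that would alter an established scale on the strength of one visible item.
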